## Abstract

**Background:**

Swedish policy states that older adults should be able to age safely with continued independence and lead active lives. However, this plays out differently in different Swedish municipalities depending upon degree of demographic change, globalization, and urbanization. Internationally, older adults living in disadvantaged areas have worse physical and mental health, activity restrictions, and reduced life expectancy. In Sweden, research on how disadvantaged areas impact older adults’ quality of life is virtually nonexistent. We argue that disadvantaged areas exist in both urban and rural contexts.

**Objective:**

We aimed to investigate how older adults’ homes and neighborhoods influence their community participation, quality of life, identity, and belonging in urban and rural disadvantaged areas in Sweden, and how these person–context dynamics are experienced by older adults in transitioning neighborhoods.

**Methods:**

The study has a mixed methods design and includes 3 phases. Adults 65 years and older living in certain urban and rural disadvantaged areas in the south of Sweden will be included. Phase 1 is an interview study in which qualitative data are collected on neighborhood attachment, identity, and belonging through semistructured interviews and photo-elicitation interviews with 40 subjects. A variety of qualitative data analysis procedures are used. In phase 2, a survey study will be conducted to explore associations between observable and self-rated aspects of housing and neighborhood (physical, social, and emotional), participation, and quality of life; 400 subjects will be recruited and added to the 40 phase-1 subjects for a total of 440. The survey will include standardized measures and study-specific questions. Survey data will be analyzed with mainstream statistical analyses and structural equation modeling to understand the interactions between quality of life, home and neighborhood factors, and sociodemographic factors. In phase 3, the integration study, survey data from the 40 participants who participated in both data collections will be analyzed together with qualitative data with a mixed methods analysis approach.

**Results:**

As of the submission of this protocol (August 2022), recruitment for the interview study is complete (N=39), and 267 participants have been recruited and have completed data collection in the survey study. We expect recruitment and data collection to be finalized by December 2022.

**Conclusions:**

With an increasing proportion of older adults, an increasing number of disadvantaged areas, and an increasing dependency ratio in more than 50% of Swedish municipalities, these municipalities are transforming and becoming increasingly segregated. This study will add unique knowledge on what it is like to be older in a disadvantaged area and deepen knowledge on housing and health dynamics in later life. Further, the design of the current study will allow future follow-up studies to facilitate longitudinal analysis (if funding is granted) on aging in a transforming societal context.

**International Registered Report Identifier (IRRID):**

DERR1-10.2196/41255

## Introduction

### Background

Inclusive and accessible living environments are fundamental to well-being, and Swedish aging policy states that older adults should be able to age safely, maintain their independence, and continue to lead active lives. However, with demographic change, globalization, and urbanization, health inequality is a growing societal challenge. The chances of older adults being able to lead a good life vary depending upon which of Sweden’s 290 self-governed municipalities they live in. There is a lack of knowledge on what it is like to age in areas where the societal challenges are most evident. International studies show that the quality of life of older adults living in disadvantaged areas is affected in many ways. They have worse physical and mental health, activity, and participation restrictions—and shorter life expectancy. In Sweden, research on how living in a disadvantaged area affects older adults’ quality of life is virtually nonexistent. We argue that disadvantaged areas exist in both urban and rural contexts, but conditions, experiences, and perceptions may be quite different. This study addresses how the home and neighborhood influence quality of life for older adults who live in urban and rural disadvantaged areas and how these person–context dynamics are experienced. In the proposed study, we will investigate urban disadvantaged areas with a high proportion of crime, social unrest, fast population turnover, and a high percentage of unemployment [1]. We will also investigate rural disadvantaged areas with a consistently decreasing population and a shrinking tax base for health and social care services [2]. We will study areas that are changing in many ways. Older adults tend not to move as often as younger adults, thus experiencing the consequences of disadvantaged areas in transition. By focusing on older adults, the results will aid in understanding how societies can ensure healthy lives, promote quality of life at all ages, and have sustainable cities and communities that provide opportunities for all.

### Disadvantaged Areas in Sweden

In 2016, the Swedish National Police published their first-ever report on what they called “socially disadvantaged areas”; the most recent report, from 2017, listed 61 areas in Sweden. According to the Swedish National Police, a socially disadvantaged area is a geographically defined urban area with low socioeconomic status, high levels of crime, fast population turnover, and a high proportion of immigrants. Residents are at risk of being excluded, feeling alienated, losing faith in the future, and having health problems. Over time, criminal networks have become increasingly present [1]. Typically, the neighborhoods are large residential areas with little traffic. Landlords are typically public housing companies, and the dwellings are rented apartments in multi-dwelling blocks. The areas have been criticized for not being well kept, needing maintenance and repairs, and being overcrowded. Lately, retail store owners have been reluctant to establish businesses in these neighborhoods, which reduces amenities. Approximately 81% of the population is of non–Swedish origin, and the proportion of older adults is smaller than the national average: approximately 12.5%, compared to 19% nationally. Of the Swedish-born population, the majority are likely older and have lived in the area for many years. For older adults, safety and security risks and not having access to local services are important concerns, as are feelings of alienation from the neighborhood. Contrastingly, other surveys show that many residents like their neighborhood and that crime rates are slowly decreasing [3]. Turning to rural areas, depopulated areas make up another supposedly disadvantaged area. Depopulated areas are municipalities or parts of municipalities that have been characterized by significant population decline for the last 20 years due to urbanization, high unemployment rates, and weak housing markets [2]. These areas also have a larger proportion of older adults than the national average: 25%, compared to 19% nationally, and due to a reduced tax base (ie, a high social dependency rate) public health and social care services are expensive to provide and facilities are sometimes closed. It is also difficult to provide small, suitable dwellings for older adults who want to downsize [2]. In these areas one finds that older adults mostly live in single-family houses, are homeowners, and were born in Sweden. Car dependency is high. Retail store owners have had a hard time keeping shops and businesses running, which reduces amenities in the area. It is likely that urban and rural disadvantaged areas are influencing older adults’ quality of life in ways that are unique to each, but also in other ways that are similar in both. An understanding of how the context influences older adults in both urban and rural disadvantaged areas is needed to reveal the heterogeneity of living conditions of older adults in Sweden.

Sweden could be described as a social democratic welfare state in transition. The Swedish population, and older adults in particular, are known to show high levels of trust toward government officials, media, and fellow citizens in general. The health care and social care systems have universal coverage, but local differences in service provision are a growing challenge to equality [4]. The wave of immigrants that entered Sweden in 2014 to 2015 has affected municipalities in rural areas (where many were placed upon arrival) and urban areas (where many settled by choice). With increasing societal challenges in Sweden and with new generations of non–Swedish born older adults living in disadvantaged areas, research on aging in Swedish disadvantaged areas can contribute to international knowledge on quality of life in later life in disadvantaged areas.

### Overview of the Research Field

In general, older adults tend to move less often than younger adults, and the home becomes an essential arena for social life with increasing age. Health and quality of life are likely more influenced by the home and neighborhood in older adults than in younger people [5]. Accessible homes support older adults in managing activities of daily living independently for longer [6]. High housing satisfaction is related to higher life satisfaction, and higher neighborhood social cohesion supports participation in activities and in society. However, we do not know whether previous findings from Swedish and European home-health-dynamics studies of older adults, which had participants who were fairly healthy and socioeconomically well-off (eg, the ENABLE AGE Project [7]), apply to older adults in disadvantaged areas. We do not know if previous findings on the importance of weak ties among neighbors apply within areas that are transitioning and have fast population turnover, as in disadvantaged areas in Sweden [8].

International reviews of older adults living in neighborhoods with low socioeconomic status (SES) show that a variety of neighborhood factors negatively impact depression, cognitive skills, and overall health [9-11]. Further, disadvantaged areas can restrict outdoor mobility possibilities for participation, and ultimately increase the risk of mortality [12-15].

Several authors conclude that there is a need for more nuanced measures of neighborhood quality, both objective and self-rated. It is also necessary to investigate contradictory results (eg, ethnic enclaves in the United States seem to have a positive effect on health for Latino populations but not for African American populations [11]) and to identify modifiable aspects of the living environment to develop interventions supporting quality of life. A meta-analysis of neighborhood effects on mortality included 11 studies from Sweden; however, none focused on older adults [15]. The authors found reduced life expectancy among residents from areas with low neighborhood SES, and they concluded that in order to better understand how social and physical neighborhood factors contribute to well-being, quantitative methods need to be complemented with qualitative methods.

Researchers on rural aging have explored the challenges older adults experience when the need for support increases, but community changes have resulted in health and social care services being closed. This research highlights the strong desire to age in place and the constant negotiations that come with such a decision.

Nevertheless, other researchers have questioned the social sustainability of depopulated areas, arguing that rural aging needs more attention [16] and that knowledge of how home and community factors interact with quality of life in rural areas is lacking.

It has been suggested that older adults are more dependent than younger adults on the home and neighborhood context and are more vulnerable to neighborhood change; however, this has not been empirically supported by recent studies. Contrastingly, it has also been suggested that older adults with lower SES might be more resilient to neighborhood stressors than older adults from areas with high SES [5]. Both of these conclusions are highly generalized, and it is thus important to explore positive aspects of living in disadvantaged areas and critically examine negative images from media to obtain a nuanced picture of the day-to-day life of older adults in disadvantaged areas.

### Theoretical Underpinnings

Acknowledging the complex individual–context dynamics and quality of life in disadvantaged areas calls for several theoretical perspectives. We ground our study in a theoretical framework of ecological theories on aging, social networks, human geography, occupational justice, and a perspective of the social life course [17-21].

Early models from Lawton and Nahemow [19] are based on an environmental gerontology perspective that usually includes aspects of the built environment and tries to explain the fit or the congruence between the capabilities of the person and the demands of the environment. We will use the concept of place-making [21], describing how older adults develop “insideness” and the process of belonging and identity in relation to a home or an area. After relocation to a new space, place-making skills might be disrupted if other changes occur as well. If the older adult cannot continue with their day-to-day habits and routines in the new dwelling, the older adult might not develop attachment.

We also add a social layer that includes identity, roles, and the norms that are created and formed within the social context. Moreover, being, acting, and meaning-making are interactive processes between the individual and the social context. The individual takes part in creating the context and the context creates the individual. The complexity of and the forces within social contexts need to be acknowledged to better understand the effects of exclusion and marginalization on disadvantaged areas and the effects of inclusion and creation of community in seemingly harsh areas [22].

The social life-course perspective explains that aging is contextual and that the journey of individuals across the life course is parallel to development and changes in the surrounding society [20]. Individuals age and change while the society they live in ages and changes, too. Older adults are likely to interpret feelings of well-being and belonging in their neighborhood in the light of ideas on the past, present, and future of their life course and the surrounding society. Further, social network theory and theories on social ties will be important in understanding how the context influences quality of life [8,18].

### Conceptual Definitions

#### Quality of Life

We use the World Health Organization Quality of Life Group definition of quality of life as a construct that captures an individual’s physical and psychological health, social relationships, and the environment and defines quality of life as an individual’s perception of their position in life in the context of the culture and value systems in which they live and in relation to their goals, expectations, standards, and concerns [23].

#### Participation

The World Health Organization defines participation as an individual’s involvement in life situations that let them take part in society [24], in addition to participation in tasks and activities that are meaningful to them (eg, occupations) and promote health, well-being, and participation in life [17].

#### Context

We define the environment surrounding the individual as their context, focusing on the home and neighborhood. This context includes physical factors (eg, buildings and spaces), social factors (eg, family, friends, neighbors, and social networks) and emotional or identity factors (eg, place attachment and belonging).

### Study Objective and Research Questions

The study objective is to investigate how home and neighborhood influence participation, quality of life, identity, and belonging of older adults living in urban and rural disadvantaged areas in Sweden, and how these person–context dynamics are experienced by older adults in transitioning neighborhoods. We have three research questions. First, how do older adults in disadvantaged areas reason about their home and neighborhood in relation to their quality of life, and how do they act on concerns regarding their neighborhoods? We will pay particular attention to ways that identity and belonging are manifested, ways that participants relate to the existing media images of the area they live in, participants’ thoughts on relocation, and how they place themselves in a transforming neighborhood context. Second, how are observable and self-rated home and neighborhood factors associated with the quality of life of older adults in disadvantaged areas? We will pay particular attention to urban/rural, gender, and Swedish born/non–Swedish born subgroup differences as potential mediators. Third, how can we contribute to existing theoretical perspectives on aging in context by contrasting and integrating knowledge of older adults’ quality of life in urban and rural disadvantaged areas?

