## Methods

### Study Design

This baseline study has an explanatory sequential mixed methods design [25] and includes 3 phases. Phase 1, the interview study, includes semistructured interviews and photo-elicitation interviews with 40 subjects). Phase 2, the survey study, will collect quantitative data via telephone survey interviews; 400 subjects will be recruited and added to the 40 phase-1 subjects, for a total of 440 subjects. In phase 3, the integration study, data from the previous phases will be combined and analyzed with a mixed methods analysis approach [25].

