### Phase 2: Survey Study

#### Power Calculation, Sample Size and Recruitment

We aim for a sample size of N=400 in phase 2. Power calculations were made based on the World Health Organization 10 Wellbeing index [27], assuming a mean difference of 4.0 with an SD of 10.0 (power 0.80 and *P*<.05), resulting in a recommended sample of at least 98 participants per area. Acknowledging that the power calculation was highly indicative, that the study design was explorative overall, and that we aimed to perform follow-up data collection (if granted funding), we decided to include 200 participants from urban areas and 200 participants from rural areas. To recruit them, we ordered lists of contact information for all adults aged 65 years or older in the targeted urban and rural areas from the SPAR and performed randomization. We will aim for a sample that includes 50% urban participants and 50% rural participants, with 50% being aged 65 to 79 and 50% aged 80 or older. In all, approximately 12,500 adults 65 years or older live in the targeted areas. Anticipating an inclusion rate of 20% or more, the randomized lists will contain a total of 2000 names. Our procedure is to send out information letters and follow up with a telephone call. If the participant meets the inclusion criteria and is willing to participate, we set a date for the telephone interview.

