### Statistical Data Analysis

For newly translated measures not before used in this context (eg, PPFM-OA [28]), preparatory analyses targeting validity and precision will be conducted before proceeding to primary analyses targeting specific research questions. The survey data will be analyzed with mainstream statistical analyses and SEM to explore and evaluate interactions between quality of life, home and neighborhood factors, and sociodemographic factors. The use of SEM will also support and question theory building.

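### Urban/rural setting, gender and country of birth are labelled potential mediators of the link between home or neighborhood and quality of life, a causal role they cannot have; they are effect modifiers or confounders.

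*Protocol article*

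**What the plan says.** In the Protocol article, under Study Objective and Research Questions, the second question asks "how are observable and self-rated home and neighborhood factors associated with the quality of life of older adults in disadvantaged areas". Exposure and outcome are therefore clear: home and neighborhood factors on one side, quality of life on the other. The next sentence singles out urban versus rural setting, gender, and being born in Sweden or elsewhere, and treats these "subgroup differences as potential mediators".

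The Statistical Data Analysis section is the only text on how the survey will be analysed. Besides mainstream methods, it plans "SEM to explore and evaluate interactions between quality of life, home and neighborhood factors, and sociodemographic factors". It names no indirect effect, mediation path, product term or multi-group comparison.

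Under Power Calculation, Sample Size and Recruitment, setting is a sampling stratum: "we decided to include 200 participants from urban areas and 200 participants from rural areas". The sample size was derived by "assuming a mean difference of 4.0 with an SD of 10.0" on a well-being index. Study Design states that "This baseline study has an explanatory sequential mixed methods design", so the survey is a single wave.

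**The concern.** A mediator lies on the path from exposure to outcome: the exposure changes it, and it in turn changes the outcome. None of the three variables meets the first condition. The sentence also conflicts with itself, because differences between subgroups are a matter of effect modification, not of an intermediate step.

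The label matters because structural equation modeling is the planned tool, and there a mediator label becomes a drawn path. Two errors would follow from a literal reading:

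- **Slope differences go untested.** The indirect effect is the product of exposure-to-group and group-to-outcome coefficients. Neither measures whether the exposure's slope differs between groups.
- **Confounding is reported as mediation.** If group membership affects both the exposure and quality of life, both coefficients are non-zero, and their product looks like an indirect effect of housing acting through setting or origin.

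The second error is the more plausible one here. The section on disadvantaged areas in Sweden describes urban areas of mostly rented apartments with a largely non-Swedish-origin population, and rural areas where older residents mostly own single-family houses and were born in Sweden.

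**Working it through.** **1. Can each variable be caused by the exposure?**

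| Variable | What the article fixes | Possible role for home/neighborhood → quality of life |
|---|---|---|
| Gender | Precedes the current dwelling | Modifier or confounder |
| Swedish-born or not | Precedes the current dwelling | Modifier or confounder |
| Urban/rural | Stratum of 200 and 200, drawn from preselected areas; at least 5 years' residence required | Modifier or confounder |

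No row allows a mediator.

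**2. What the label would do if followed.** The re-derivation used a simulation with N=400, 200 per group and 1000 runs per scenario. All effect sizes are assumed. The mediation test required both exposure→group and group→outcome (given exposure) to be significant at 5%. The alternative was the exposure-by-group product term.

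| Scenario | Mediation test significant | Product term significant |
|---|---|---|
| Slope 0 in one group, 0.4 SD in the other; same exposure mean | 0.1% | 97.4% |
| Group is only a common cause: shifts exposure by 0.5 SD and outcome by 0.4 SD; slope 0.2 in both | 97.1% | 5.2% |

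The first row needs equal exposure means. Given the housing differences that the article describes, that is unlikely for tenure and dwelling type, so the second row is the better guide for those factors.

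**3. The article's own sample size.** Inputs: difference 4.0, SD 10.0, power 0.80, 5% level (two-sided assumed).

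- n per area = 2 × (1.96 + 0.84)² × (10/4)² = 2 × 7.85 × 6.25 ≈ 98. The t-test version gives 99.08, and power at 98 per area is 0.7996. The stated 98 is reproduced.
- At 200 per area, power for the same mean difference is about 98%.

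This figure covers a comparison of two means and no subgroup contrast.

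**4. What the sample supports for effect modification.**

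*Difference in correlation between two groups, Fisher z scale:*
- 200 vs 200: SE = √(1/197 + 1/197) = 0.101; detectable at 80% power = 2.80 × 0.101 ≈ 0.28.
- If the 440 split 220 vs 220 (assumed): √(2/217) = 0.096; × 2.80 ≈ 0.27.
- If origin split 80 vs 320 (assumed; the article gives no split for the sample): √(1/77 + 1/317) = 0.127; × 2.80 ≈ 0.36.

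These are z units. A z difference of 0.28 starting from r = 0.10 reaches tanh(0.100 + 0.28) = 0.36, a difference of about 0.26 in r. Starting from r = 0.40 it reaches tanh(0.424 + 0.28) = 0.61, a difference of about 0.21.

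*Difference of differences, with group and a dichotomised factor in four equal cells (assumed), SD 10:*
- N=400: SE = 10 × √(4/100) = 2.0; power for an interaction of 4.0 is Φ(4.0/2.0 − 1.96) ≈ 52%; detectable at 80% power ≈ 5.6.
- N=440: SE = 10 × √(4/110) = 1.91; power ≈ 55%; detectable ≈ 5.3.

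**The case against.** The strongest reply is that this is a slip of one word in an introductory research question. Subgroup differences is moderation language, and the analysis section speaks of methods "to explore and evaluate interactions between quality of life, home and neighborhood factors, and sociodemographic factors", which is nearer to effect modification than to mediation. The study also calls itself explorative overall and its power calculation highly indicative, and no decision rule hangs on the sentence.

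Much of this stands. A reader might infer that the subgroup question is going to be tested with the wrong model. The article does not support that: no mediation model appears anywhere, and the details of the structural equation model may properly sit in a fuller plan. Nor is the absence of invariance testing or of a model diagram a defect in an article.

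The analysis section nevertheless does not cure the label. Its list of things that interact includes the outcome itself, so the word is used loosely and defines no product term.

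One might also argue that housing influences where people live, so that setting could follow from the exposure. But the factors in question are those of the current home and neighborhood, measured in residents sampled because they already live there. It is also possible that home and neighborhood factors were meant to mediate differences between urban and rural residents. That would be coherent, but it reverses the roles that the sentence gives.

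**Conclusion.** The stated role is wrong and should be corrected. For gender and country of birth this follows from time order, and for setting from the sampling; neither rests on an assumed number. The consequences are conditional: they arise only if the sentence is carried out literally in the structural equation model. The simulated 97.1% and 0.1% show the direction of the errors under assumed effects and do not predict this study's results.

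Two stronger inferences should be avoided. Origin and setting probably overlap because of who lives in the areas, but the design does not impose this: recruitment balances setting and age, not origin. And 0.28 is a Fisher z difference, not a difference in correlations.

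The severity is moderate. The point concerns the study's quantitative research question and three comparisons singled out for particular attention, but in an exploratory survey where a wording change and a matching analysis statement resolve it.

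**What to change.** In the second research question, replace the mediator label with *potential moderators (effect modifiers)*. In the analysis section, state that:

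- effect modification by setting, gender and country of birth will be tested with exposure-by-group interaction terms or multi-group structural equation modeling;
- the same three variables will be adjusted for as confounders when overall associations are estimated;
- these contrasts are exploratory, since the sample size was set only for a mean difference between areas.

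If a mediation question is also wanted, it needs a variable that the home or neighborhood can influence. Participation, which the survey already measures, is one candidate; with a single wave, any indirect effect should be labelled exploratory.

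The cost is one wording change, a short addition to the analysis text and some extra analysis work. No new data are needed. The downside is limited power for the subgroup contrasts, which the exploratory label makes plain.
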